### Who will take informed consent? {26a}

This study will be conducted within one site in the country of Singapore. As this study will recruit patients who are experiencing terminal delirium, the patients would fulfil the definition of lacking mental capacity under Section 4 of the Mental Capacity Act, “a person who lacks capacity is one who lacks mental capacity in relation to a matter, if at the material time, this person is unable to make a decision for own self in relation to the matter because of an impairment of, or a disturbance in the functioning of, the mind of brain.” [7]

For this study, a proxy (or person responsible) for the patient would be approached to provide consent on behalf of the patient. Proxy consent was suggested as a suitable method for consent collection, given the patient’s absent or fluctuating capacity to consent. It was successfully used in dementia and delirium research and was reported to have been acceptable to patients and their caregivers [8]. In most situations, the proxy will also be the primary caregiver, who will administer the medication dosages per instructions, monitor the patient, and ensure that the patient’s care needs are met. However, there are exceptions in which the proxy and caregiver are separate individuals. In this case, the identified caregiver will be included during consent-taking and receive the participant information sheet.

Section 7 of the Human Biomedical Research Act [9] states that, where there is a need to recruit adults who lack mental capacity, appropriate consent for the adult must be obtained via a valid proxy, either:

(i)From a donee or deputy (if existing or in force, to be verified in ways feasible by the research team at the time) who is authorised to give consent to the biomedical research on behalf of the adult, or(ii)In the case where there is no pre-designated donee or deputy, consent is obtained from any of the following persons, in the following order of priority:
SpouseAdult childParent or GuardianAdult siblingAny other person named by the adult as someone to be consulted on the matter in question or on matters of that kind.

The proxy for the patient will be approached by a study team member who does not provide direct medical or hospice care to the patient. This is to reduce the risk of compulsion through an established patient-provider relationship. The member will provide more detailed information about the study to the proxy. If agreeable, the proxy will sign the informed consent form and the patient will be recruited into the study. The proxy can refuse to participate, with no compromise to the patient’s care; the patient’s primary palliative care team will continue to provide medical care and hospice support in the usual way outside of a research study. The study team will assure the proxy of this fact before informed consent is collected.

### Additional consent provisions for collection and use of participant data and biological specimens {26b}

Not applicable.

## Interventions

### Explanation for the choice of comparators {6b}

Haloperidol and olanzapine are two antipsychotic drugs commonly used by palliative care clinicians. Haloperidol is an older drug that has been used historically, while olanzapine is a newer option, purportedly for its lower side effect profile [3]. One recent study compared haloperidol and olanzapine injections in 100 hospitalized patients and found that they were similar in efficacy, as well as safety [10].

The dosage of haloperidol varied across previous studies on terminal delirium management with a general range of 1.5-15 mg per day. However, lower dose of haloperidol regime showed no significant benefit in reducing the severity of delirium symptom; a study by Li n[11] found that the loading doses were 5 mg and titrated to 10 mg per day with a maximum dose of 15 mg/day. This has led to a significant improvement of delirium rating scale across time periods. In our study design, the doses of OT haloperidol for the assigned group of patients are 5–10 mg per day based on the symptom burden.

Current published evidence for the dose of olanzapine in managing terminal delirium is scarce although it has been increasingly used for general delirium treatment with a recommended dose of 2.5–30 mg per day. The equivalent dose for the first- and second-generation antipsychotics based on 100 mg chlorpromazine are 1.5–2 mg haloperidol to 4–5 mg olanzapine [12]. In our study, the doses of OT olanzapine for the assigned group of patients are 10–20 mg per day.

Other than injections, both medications can be administered in oral transmucosal forms. This route of administration is an important option for patients in the community care setting; in many situations, the caregiver would be responsible for administrating medication. However, they may not be trained to provide injections or may feel that injections are distressing. OT administration serves as a more viable, less stressful and safer alternative.

No evidence is available for comparing efficacy between these two drugs in this route of administration. This serves as the impetus for the study.

### Intervention description {11a}

Every 24 h, patients will receive two regular doses of either OT haloperidol 2.5 mg or OT olanzapine 5.0 mg with an interval of 12 h. Patients may also receive up to two breakthrough doses within a minimum interval of 1 h from the last dose when needed. In total, up to four doses of medication will be prepared. The dosage schedule is provided below in Table 2.

**Table 2 Tab2:** Dosage schedule for clinical trial

	Timing	Haloperidol	Olanzapine
First 24 h	First dose	2.5 mg	5.0 mg
	12 h later	2.5 mg	5.0 mg
	First breakthrough	2.5 mg	5.0 mg
	Second breakthrough	2.5 mg	5.0 mg
Second 24 h	First dose	2.5 mg	5.0 mg
	12 h later	2.5 mg	5.0 mg
	First breakthrough	2.5 mg	5.0 mg
	Second breakthrough	2.5 mg	5.0 mg
Third 24 h	First dose	2.5 mg	5.0 mg
	12 h later	2.5 mg	5.0 mg
	First breakthrough	2.5 mg	5.0 mg
	Second breakthrough	2.5 mg	5.0 mg
	Total dose prepared	30.0 mg (10.0 mg/day)	60.0 mg (20.0 mg/day)

The haloperidol preparation is a solution with concentration of 2 mg/mL of haloperidol. The medication is administered via dropper, where 20 drops is equal to 1 mL (1 drop = 0.05 mL). Standardized doses of 2.5 mg of haloperidol (25 drops or 1.25 mL) of the haloperidol preparation would be administered for each dose.

Olanzapine preparation is a 5 mg oro-dispersible tablet. Standardized doses of 5 mg will be delivered each time a dose is required.

After obtaining consent, the patient will be randomized into either the haloperidol or olanzapine group. Instructions on how to administer the medication will be provided to the caregivers; caregivers will also be advised to serve breakthrough doses of the assigned anti-psychotic drug as needed. Basic demographic information, including the patient’s age, sex, primary diagnosis, and co-morbidities, will be collected.

All relevant trial materials are prepared in packs with the following materials:
The required amount of medication (haloperidol or olanzapine),Rescue medication—subcutaneous midazolam with syringe and needle,A copy of the patient information sheet and informed consent form,Instructions for the caregivers on how to administer medication, andA copy of the case report form.

The investigators will provide the packs to the caregivers of enrolled patients. Additionally, the investigators will conduct daily clinical reviews at home over 72 h. They will confirm that the dosages used and the dosages documented are congruent.

Subcutaneous injectable midazolam would be prepared as a rescue medication in the event delirium symptoms remain uncontrolled and distressing after the trial medication is depleted. Rescue medications will be used in any one of the following situations:
Within any of the 24-h periods, the patient remains uncontrollably agitated, despite all prepared doses of the treatment having been applied.Patient is unable to tolerate OT medication.Patient experiences severe toxicities from trial medication.

The caregiver will receive detailed instructions for the trial included with the case report forms. The forms will also provide support resources such as the hospice hotline and investigators’ contact number. Per clinical practice, the caregiver will give the first dose of medication under the supervision of the study team. Additionally, they will be instructed on how to rate the patient’s agitation and will provide the baseline rating with the investigator’s support. The study team physician will assess the patient’s baseline symptom severity.

Alongside drug therapy, usual non-pharmacological interventions will be provided to all patients. These interventions include (i) regularly orientating the patient; (ii) keeping the room bright during the day; (iii) minimizing the use of tubes, catheters, physical restraints, or other immobilizing devices; and (iv) minimizing unnecessary disturbances to the patient.

### Criteria for discontinuing or modifying allocated interventions {11b}

The study will be terminated for that patient in any one of the following situations:
Midazolam injectable rescue medication is used, or the allocated daily dosage limit is reached.Toxicities related to the trial medication were observed to be intolerable.Proxy asks to withdraw the patient from the study.Patient is admitted to the hospital.

The study may be terminated at any point during the trial. In that event, the investigators will record the reason for cessation, and make a final assessment of the patient, where applicable. The patient will continue to receive support from their palliative care providers. Data from the patient will be included for analysis up to the point of discontinuation; subsequent time points will not include that patient.

The proxy or the patient may choose to withdraw participation from the study at any time, without compromising further treatment using other drugs or alternative dosage regimen. The patient’s primary palliative nurse will be informed, and they will continue to arrange and provide medical care and hospice support for the patient, in the usual way outside of research. They will advise how persisting symptoms should be managed, outside of the study.

If voluntary withdrawal occurs, the patient will be asked to continue scheduled evaluations, complete an end of study evaluation, and be given appropriate care under medical supervision until the symptoms of any adverse event resolve or the patient’s condition becomes stable.

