### Strategies to improve adherence to interventions {11c}

Instructions for how to administer medication will be provided to the caregivers by the investigators. Moreover, the patients and their caregivers have access to a 24/7 on-call service, which they can call to make clarifications and to receive medical support when needed.

At each time-point (i.e. daily), the investigators will conduct a home visit to ensure that the medication has been appropriately administered and that the ratings have been recorded.

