#### The Memorial Delirium Assessment Scale

MDAS is a ten-item, four-point clinician-rated scale designed to quantify the severity of delirium in medically ill patients [13]. It has very good psychometric properties, with high reliability (*r* = .91) and good discriminant and concurrent validity. Though the scale was intended to assess patients based on all ten items, it was suggested that items in MDAS can be pro-rated in the event the patient is not able to communicate (Lawlor, et al., 2000). To conduct assessments as well as to ensure patient’s safety, the study team physician will make regular home visits to assess the patient at the time of the first dose, and then at 24 h, 48 h, and 72 h after the first dose.

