### Methods in analysis to handle protocol non-adherence and any statistical methods to handle missing data {20c}

Given the unstable state of the patient, and the community setting being a more difficult-to-control environment, protocol non-adherence may occur due to a variety of real-world factors. The investigators will document instances of non-adherence and assess if the patient would need to be withdrawn from the trial; patient safety and comfort would be prioritised.

To handle protocol non-adherence, analysis will be done on an intention-to-treat analysis basis; participants would be classified according to the treatment they were originally randomised. This analysis method would best reflect the original trial design.

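### As worded, taking the fourth daily dose that Table 2 permits ends the patient's study and removes later MDAS scores

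*Protocol article*

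**What the plan says.** All references are to the protocol article.

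- **Stopping rule (Criteria for discontinuing or modifying allocated interventions {11b}).** The first of the listed triggers is: "Midazolam injectable rescue medication is used, or the allocated daily dosage limit is reached". The consequence for the data is: "Data from the patient will be included for analysis up to the point of discontinuation; subsequent time points will not include that patient". A final assessment is made at cessation where applicable.
- **Regimen (Intervention description {11a}).** Two regular doses are given every 24 hours. In addition, "Patients may also receive up to two breakthrough doses within a minimum interval of 1 h from the last dose when needed". Table 2 lists these four doses for each of the three 24-hour periods and totals them at 10.0 mg (haloperidol) or 20.0 mg (olanzapine) per day.
- **Dose range (Explanation for the choice of comparators {6b}).** Haloperidol is planned at 5–10 "mg per day based on the symptom burden", olanzapine at 10–20 mg per day.
- **Rescue (Intervention description {11a}).** One reason for midazolam is that, within a 24-hour period, "the patient remains uncontrollably agitated, despite all prepared doses of the treatment having been applied". The other two are inability to tolerate the oral route and severe toxicity.
- **Analysis set (Methods in analysis {20c}).** The analysis is by intention to treat: "participants would be classified according to the treatment they were originally randomised".

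**The concern.** The stopping rule and the regimen do not fit together. The second breakthrough dose of a day is an ordinary part of the allocated treatment, yet giving it is also the event that ends the patient's study. A patient who is settled by that dose and never needs midazolam would still have no further scheduled MDAS scores analysed.

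The rule also conflicts with the rescue provision. Midazolam for agitation is allowed only once the doses prepared for the period are used up. By then the dose-limit trigger has already ended that patient's study.

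Primary-outcome data are at stake. Breakthrough doses are given as needed, so the patients who lose later scores are mainly those whose symptoms are harder to control. If one drug controls symptoms less well, more of its patients leave the later time points. Classifying patients by randomised arm does not bring those scores back. The upper end of the stated dose range would also be thinly represented at 48 h and 72 h.

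**Working it through.** **1. What the daily limit is.** The term is not defined elsewhere, so Table 2 is the only candidate. Its figures reproduce:

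- Haloperidol: (2 regular + 2 breakthrough) × 2.5 mg = 10 mg/day; × 3 days = 30 mg.
- Olanzapine: 4 × 5 mg = 20 mg/day; × 3 days = 60 mg.

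Both match the table. The fourth dose of a period is the one that reaches the limit.

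**2. How much of the prepared supply a patient can use and still stay in to 72 h.**

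- Below the limit every day: 3 × 3 = 9 of 12 doses, which is 9 × 2.5 = 22.5 mg or 9 × 5 = 45 mg.
- If a final assessment in the third period counts as the 72 h score: 3 + 3 + 4 = 10 doses, which is 25 mg or 50 mg.

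**3. Which scores are lost, by the period in which the fourth dose falls.**

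| Fourth dose in | Scheduled scores lost | Possibly replaced by the final assessment |
|---|---|---|
| Period 1 | 48 h and 72 h; also 24 h if not yet taken | 24 h |
| Period 2 | 72 h; also 48 h if not yet taken | 48 h |
| Period 3 | 72 h if not yet taken | 72 h |

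**4. How many patients keep all three post-dose scores.** Let *f* be the fraction per 24-hour period who reach the fourth dose or receive midazolam. The document gives no value, so *f* is assumed, taken as independent across days, with deaths ignored. The recruitment target is 80 (Table 3).

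| *f* | 80 × (1 − *f*)³, final assessment not counted | 80 × (1 − *f*)², final assessment counted |
|---|---|---|
| 5% | 68.6 | 72.2 |
| 10% | 58.3 | 64.8 |
| 20% | 41.0 | 51.2 |

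Table 3 asks for 64 patients, and 64/80 = 0.80. The count falls below 64 when *f* exceeds 1 − 0.8^(1/3) = 7.2%, or 1 − 0.8^(1/2) = 10.6% if the final assessment counts.

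**5. Illustration of bias in the 72 h difference (haloperidol minus olanzapine).** Only the SD of 7.64 and the baseline mean of 18 come from the protocol. The other inputs are assumptions:

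- Olanzapine means are 18, 14, 12 and 10.5 at the four visits. Haloperidol is 2 points or 0 points higher after baseline.
- Correlation between visits is 0.5 or 0.7.
- The fourth dose is triggered when MDAS exceeds a threshold met by 20–40% of the olanzapine arm by 72 h. One to two thirds of that share receive midazolam.
- There are 400,000 simulated patients per arm.

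| Handling, true difference 2 | Raw 72 h score | Change from baseline |
|---|---|---|
| Rule as worded | 0.93–1.31 | 1.78–1.96 |
| Cut at midazolam only | 1.10–1.62 | 1.88–1.98 |
| All scores kept, midazolam lowers MDAS by 4–8 | 1.18–1.82 | 1.19–1.84 |

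Under the rule as worded, 48–71% of the haloperidol arm and 60–80% of the olanzapine arm are still in at 72 h. If midazolam instead raises MDAS by 4 points, keeping all scores gives 2.16–2.42. With no true difference, every handling gives between −0.05 and 0.03.

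Two milder versions of the rule as worded were also tried. If the trigger correlates only 0.5 with MDAS (assumed), the change-score result is about 1.9–2.0. If the final assessment counts, it is about 2.0 even with the MDAS-driven trigger.

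**The case against.** **The intended meaning may be narrower.** Supplying four doses for each of three periods makes little sense if the fourth ends the study. The sponsor may have meant that the limit is reached with symptoms still uncontrolled. That is plausible, but the text joins two triggers with *or* and says only that the limit is reached. In an open-label trial with caregiver-administered doses, different team members could apply it differently.

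**The data are not wholly discarded.** Everything up to discontinuation is kept, and a final assessment may be made. This stands, and it is why ranges are shown.

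**A serious bias is not shown.** A reader might infer that the rule badly distorts the comparison or hides an inferior haloperidol arm. The document does not support that. The primary outcome is reduction in MDAS, and the statistical methods section analyses changes. On change scores the illustration loses little of a true 2-point difference and creates none where there is none. The large attenuation appears only on raw 72 h scores. The simulation is also severe, because it triggers on MDAS itself. In the protocol, caregivers give breakthrough doses as needed and midazolam for symptoms follows agitation, while a physician rates MDAS separately. The missingness is related to symptom control, but it is too strong to say that MDAS determines it.

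**Falling below 64 is not established.** The trigger rate is assumed, and Table 3 already includes an attrition allowance.

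**Truncating at midazolam is not itself an error.** A reader might infer that it breaches intention to treat and that post-rescue scores must be primary. The protocol defines intention to treat as classification by randomised arm, which truncation respects. Stopping at rescue or analysing through it is a choice of question. Post-rescue scores can also move the difference either way, and in a non-inferiority trial shrinkage favours haloperidol.

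**Conclusion.** The conflict in the text is real. As worded, reaching four doses in a day, which the regimen and planned dose range allow in every period, ends the patient's study and removes later scores of the primary outcome. This happens even without rescue, and the loss is related to symptom control.

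The size is uncertain. For an assumed 5–20% per day meeting either trigger, about 41–72 of 80 patients would have all three post-dose scores before deaths. Bias on change scores is probably small, and the document fixes neither its direction nor its size. The case for change rests on the contradiction and on avoidable loss of scores that cannot be collected later in dying patients. It does not rest on a demonstrated bias. The wording should be corrected, and confidence in the practical impact is moderate because the rate and the intended meaning are both unknown.

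**What to change.** **Main change.** In the discontinuation section {11b}, delete the dose-limit half of the first trigger. Reaching four doses alone then neither ends the patient's study nor removes later scores.

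**Supplement.**

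- After midazolam, stop the trial drug but continue the 24, 48 and 72 h MDAS assessments where feasible. Visits are already planned: "At each time-point (i.e. daily), the investigators will conduct a home visit", and for MDAS "the study team physician will make regular home visits to assess the patient at the time of the first dose" and daily thereafter. The protocol already asks voluntary withdrawals to continue scheduled evaluations.
- Report an all-scores intention-to-treat analysis beside the analysis truncated at rescue.
- Show fourth-dose and midazolam use by arm.

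**Cost.** This needs a protocol amendment, reviewed by the IRB and then submitted to HSA, plus one extra analysis. There would be some additional assessments of sedated patients, some with pro-rated MDAS items. Scores after rescue include the midazolam effect and may shrink or enlarge the difference, so the all-scores analysis should not stand alone.

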### Outcomes {12}

The primary outcome is the reduction in delirium severity as measured with the Memorial Delirium Assessment Scale (MDAS). Secondary outcomes are the reduction in the severity of agitation as measured with the Richmond Agitation-Sedation Scale modified for palliative care (RASS), and the frequency and severity of medication toxicities, as measured using the National Cancer Institute Common Terminology Criteria for Adverse Events (NCI-CTCAE). These data will be collected over four time-points: (i) baseline, (ii) 24 h after commencement, (iii) 48 h after commencement, and (iv) 72 h after commencement.

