### Sample size {14}

Based on validation studies by Breitbart et al. [13] and Lawlor et al. [14], the mean scores from the Memorial Delirium Assessment Scale for patients with delirium is roughly 18 (SD = 7.64). Jain et al. [10] reported that using either haloperidol or olanzapine led to a nearly 55% reduction in patients’ MDAS score (7–8 points). Based on this, we estimate 2 points to be the minimal important difference between haloperidol and olanzapine; a 2-point difference between the treatment arms is equivalent to a 25% difference in the reduction of a patient’s MDAS score. Table 3 details sample size calculations, using the parameters as presented above.

**Table 3 Tab3:** Sample size calculation for repeated measures design

Sample size calculation for repeated measures design	
Standard deviation (drawn from literature review)	7.64
Estimated minimal important difference (effect size)	2
Target power (1-β error probability)	.80
Target *alpha*	.05
Estimated required size per treatment arm	32
Estimated minimum sample size for two arms	64
Target recruitment size (accounting for 30% attrition)	80

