## Assignment of interventions: blinding

### Who will be blinded {17a}

This study was designed as an open-label study and thus there was no blinding between trial participants, care providers or the researchers.

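### Patients given midazolam for uncontrolled agitation drop out of later MDAS and RASS time points and are counted in no outcome, which can make the arms look more alike than they are

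*Protocol article*

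**What the plan says.** Under Criteria for discontinuing or modifying allocated interventions {11b}, the first situation that ends the study for a patient is: "Midazolam injectable rescue medication is used, or the allocated daily dosage limit is reached". The same section fixes how the data are used: "Data from the patient will be included for analysis up to the point of discontinuation; subsequent time points will not include that patient". It also says that "the investigators will record the reason for cessation" and provides for a closing assessment when one can be made, without naming an instrument. Continued scheduled evaluations are promised only after voluntary withdrawal.

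Intervention description {11a} lists three triggers for midazolam. One is that "the patient remains uncontrollably agitated, despite all prepared doses of the treatment having been applied"; the others are intolerance of the transmucosal route and severe toxicity.

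Outcomes {12} and Statistical methods {20a} cover MDAS (primary), RASS, and CTCAE toxicities. Neither includes rescue use or treatment failure. The section on non-adherence and missing data {20c} specifies intention-to-treat, meaning that patients are classified by the arm to which they were randomised. Objectives {7} describes a non-inferiority trial of haloperidol against olanzapine.

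**The concern.** A patient who is still uncontrollably agitated after every permitted dose is a treatment failure. Under {11b} that patient contributes nothing to later time points, so the 48 h and 72 h means describe the patients who had not failed. If one arm fails more often, its later mean is the more flattered, and the difference between arms shrinks.

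In a superiority trial, shrinkage towards no difference usually costs power. Here it runs in the direction of the conclusion sought. The intention-to-treat statement does not help, because it assigns patients to arms but does not bring back the scores that {11b} leaves out. With no failure count among the outcomes, the planned results could not separate similar symptom control from similar scores among those who remained.

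**Working it through.** The plan gives no figure for this point, so there is none to reproduce. The calculations below are illustrations. Failure rates, improvement at exit and correlations are assumptions.

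**Inputs from Sample size {14}:** mean baseline MDAS 18, SD 7.64; expected reduction 7 to 8 points; the margin of interest from "we estimate 2 points to be the minimal important difference between haloperidol and olanzapine"; target recruitment 80, hence 40 per arm at 1:1.

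**1. Mixture calculation at a late time point.** Let R be the mean reduction in patients still in the study (7 or 8, equal in both arms, so the observed difference is 0). Let r be the mean reduction at exit in failures (assumed between 0 and R/2).

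Hidden difference = (failure proportion, worse arm − better arm) × (R − r)

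| Gap in failure | R=8, r=0 | R=7, r=0 | R=8, r=4 | R=7, r=3.5 |
|---|---|---|---|---|
| 0.20 | 1.6 | 1.4 | 0.8 | 0.7 |
| 0.10 | 0.8 | 0.7 | 0.4 | 0.35 |

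Worked case: 18/40 v 10/40 failures, R = 8, r = 0. Over all patients the mean reductions are 22 × 8/40 = 4.4 and 30 × 8/40 = 6.0, a difference of 1.6. Among patients still in the study they are 8 and 8.

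Gap needed to hide the full 2 points: 2/8 = 25% or 2/7 = 28.6% if failures had not improved; 2/4 = 50% or 2/3.5 = 57.1% if they had improved by half.

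**2. A different model, to check direction.** Assume a true 2-point disadvantage for haloperidol (means 12.5 v 10.5, where 10.5 = 18 − 7.5) and SD 7.64 at both 24 h and 72 h. Patients whose 24 h score exceeds a threshold common to both arms are removed from 72 h. The simulated 72 h difference among those remaining is:

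| 24 h–72 h correlation | 10% fail overall (7.7% v 12.3%) | 20% (16.4% v 23.6%) | 30% (25.5% v 34.5%) |
|---|---|---|---|
| 0.5 | 1.73 | 1.57 | 1.49 |
| 0.7 | 1.60 | 1.41 | 1.27 |
| 0.9 | 1.52 | 1.24 | 1.09 |

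With everyone kept, the difference is 2.0. Removal takes away about 0.3 to 0.9 points.

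**3. Precision of a failure comparison.** 95% half-width = 1.96 × √(2p(1 − p)/n). With n = 40 per arm: p = 0.30 gives 0.201, p = 0.10 gives 0.131, p = 0.40 gives 0.215. With n = 32 and p = 0.30 it is 0.225.

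**The case against.** Several objections have force.

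- **Earlier scores are kept.** A patient who fails after 24 h still has a 24 h MDAS, and the analysis spans three 24-hour periods. The figures above therefore describe a late time point, not the whole repeated-measures comparison. This stands.
- **The exit assessment may capture the failure.** This mitigates only in part: no instrument is named, and later time points still omit the patient.
- **The trigger is agitation, which RASS measures.** RASS charted up to exit may show the agitation, but it does not count failures, and the effect on MDAS is assumed.
- **Deaths are ignored in the arithmetic.** They will be a major cause of missing later scores in these patients. This also stands.
- **Counting failures could be left to a full analysis plan.** Tabulating exits by reason could be. The exclusion of these patients from later time points could not be so described: it is a rule stated in the protocol.

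Some stronger readings are tempting but not supported. A reader might infer that the result is biased towards haloperidol. Nothing says haloperidol will fail more often, and if olanzapine did, the same rule would hide an advantage of haloperidol. A reader might count every dose-limit exit as an efficacy failure, but someone controlled on the four doses that Table 2 permits in a day also reaches the limit. Nor do {11a} and {11b} contradict each other on that limit, since one governs rescue and the other stopping. Finally, symptom-driven breakthrough dosing by unblinded caregivers is part of both regimens, and leaving the dose count out of the outcomes is not a defect.

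**Conclusion.** The point holds in a limited form. The {11b} rule removes patients from later MDAS and RASS time points for a reason that includes efficacy failure, and no listed outcome counts those failures. Where the less effective arm fails more often, this can favour the conclusion of equal effectiveness.

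The size cannot be derived from the protocol. Under the assumptions shown, gaps in failure of 10 to 20 percentage points hide roughly 0.35 to 1.6 MDAS points at a late time point. Hiding the full 2 points takes a gap of at least 25 percentage points even if failures had not improved at all. This is enough to affect how a close result is read, but it does not show that the trial will reach a wrong conclusion.

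**What to change.** 1. Add a secondary outcome to {12} and {20a}: in all randomised patients, by randomised arm, the proportion with efficacy failure by 24, 48 and 72 h, with a 95% CI for the difference. Define efficacy failure as midazolam given for agitation or delirium uncontrolled after all prepared doses. Report separately dose-limit exits without persistent symptoms, midazolam for intolerance or toxicity, and deaths without failure.

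2. State in {11b} that the final assessment at exit includes MDAS. Add a sensitivity analysis in which efficacy failures stay in the later time points, once with that exit score and once with no improvement from baseline. The second version is useful because an exit score may be taken after midazolam has been given. Read the primary MDAS result alongside both the failure proportions and this analysis.

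Breakthrough doses per 24 h may be described by arm, but this is optional.

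The cost is small. Reasons for cessation are already recorded, doses are checked at daily visits, and breakthrough times are charted. What is added is MDAS at exit and some analysis. No dose or treatment rule changes. The limits are that the failure difference is known only to about ±20 percentage points (40 per arm, 30% failure assumed), and that failure is itself judged open-label, since "there was no blinding between trial participants, care providers or the researchers".
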